#### Mechanistic study

Brain Magnetic Resonance Imaging (MRI) scans and blood samples will be acquired at baseline and 12 weeks. MRI data will be acquired at 3 Tesla at 3 centres, and will include proton magnetic resonance spectroscopy (1H-MRS) to measure levels of glutamate, GSH and other brain metabolites visible in the 1H-MRS spectrum in voxels positioned in the bilateral anterior cingulate cortex and right striatum, arterial spin labelling to measure rCBF and T1-weighted structural brain images to provide anatomical localisation, grey matter masking of rCBF images and correction of 1H-MRS data for voxel tissue composition. The blood samples will be used to measure levels of peripheral pro- and anti-inflammatory cytokines and GSH.

### Sample size

The standardised mean difference for clozapine versus other antipsychotics in adults based on PANSS total score at 12 weeks is 0.39 [55]. The standard deviation of the PANSS score at 12 weeks in our similar sample of treatment resistant patients being started on clozapine [43] is 14.2 (60% CI 12.96–16.20). Using an upper limit of the 60% confidence interval [56], an effect size of 0.39 corresponds to a between group difference of 6.4 points. In our previous research [43], the 95% CI for the baseline-12-week correlation in the sample was 0.553 to 0.880, and we use a value of 0.5. This is conservative but realistic, since the time points are only 12 weeks apart. Under these assumptions, and assuming 20% attrition to 12-week follow-up, the target sample size to recruit at baseline is 260 participants.

For the mechanistic study we estimate that, of all participants recruited at MRI sites, 50% will agree to participate in MRI. This results in a sample for the mechanistic study of 90 participants at baseline and, assuming 20% attrition, complete mechanistic data in 70 participants. This sample size has 80% power to detect a minimum between group effect size of 0.7SD on a standardised scale and 90% power for 0.8SD. In our previous observational study in TRS [43], we found a within-group effect after 12 weeks of clozapine of 0.7. Assuming there is no further change from prior treatment in the standard antipsychotic treatment arm on these measures over 12 weeks, we would have sufficient power to detect between-group effects of these magnitudes and expect the effect sizes to be greater in the younger population.

### Randomisation

Participants will be randomised 1:1 using an online system hosted by the King’s Clinical Trials Unit, using computer generated blocks of random sizes. The sample will be stratified by sex and age group (< 18 years, >  = 18 years).

### Blinding

The raters for primary outcome (PANSS) and CGI-S and CGI-I will be centralised and blinded to minimise observer bias. The participants, the treating team, and the rest of the trial team will not be blinded. There will be four blinded members of the study team: two research psychiatrists, one for adult participants and the other for child participants (each with appropriate training for that age group), the Chief Investigator (CI) and Co-Chief Investigator. They will not be informed which treatment arm the participants are in and will not enquire about the participant’s treatment or side effects.

### Data collection methods and management

A web based electronic data capture (EDC) system will be designed, using the InferMed Macro 4 system. The EDC will be created in collaboration with the trial analyst and the CI and maintained by the King’s Clinical Trials Unit for the duration of the project. It will be hosted on a dedicated server within King’s College London. The system is compliant with FDA 21 CFR part 11 and Good Clinical Practice (GCP). The CI will act as custodian for the trial data. Should a participant decide to withdraw from the study, all efforts will be made to report the reason for withdrawal as thoroughly as possible. Should a participant withdraw from study drug only, efforts will be made to continue to obtain follow-up data, with the permission of the participant.

### Ethics and regulatory approvals

The trial will be conducted in compliance with the principles of the Declaration of Helsinki (1996), the principles of GCP and in accordance with all applicable regulatory requirements including but not limited to the Research Governance Framework and the Medicines for Human Use (Clinical Trial) Regulations 2004, as amended in 2006 and any subsequent amendments. The trial has been approved by London—Dulwich Research Ethics Committee (REC reference: 22/LO/0723) and obtained Clinical Trial Authorisation (CTA) from the Medicines & Healthcare products Regulatory Agency (MHRA; CTA 22926/0007/001–0003).

### Statistical analysis

The Statistical Analysis Plan will be drafted within 6 months after recruitment starts and will be approved by the Data Monitoring Committee (DMC) and Trial Steering Committee (TSC) before the junior statistician sees any outcome data split by arm. The senior statistician will remain fully blind throughout the study.

We will report data in line with the CONSORT 2010 statement [57] showing attrition rates and loss to follow-up. The target estimand is the treatment policy estimand, and all primary and secondary analyses will be carried out following the intention to treat principle, incorporating data from all participants including those who do not complete treatment. Every effort will be made to follow up all participants in both arms for research assessments. The trial will be blind rated to minimize observer bias. The primary analysis will be conducted after the final 12-week follow-up assessment is completed for the final patient recruited into the study. The study team including CI and trial statisticians will be aware of the results of the primary analysis from this point. The remaining 24-and 52-week assessments will continue to be conducted blind to individual patient’s allocation. We will analyse the 24- and 52-week outcomes in a secondary analysis.

Analyses will be conducted in Stata version 17or later. Descriptive statistics within each randomized group will be presented for baseline values. For the primary analysis, the treatment effects on primary and secondary outcomes will be estimated using linear mixed models fitted to all outcome variables up to and including the 12-week assessment. Fixed effects will be sex, age (< 18, >  = 18) and duration of previous treatment (± 3 years), baseline assessment for the outcome under investigation, treatment, time, and time*treatment interactions. Participant will be included as a random intercept to account for repeated measures. Marginal treatment effects will be estimated for primary outcome (PANSS score at 12 weeks), and for PANSS scores at each other time point (6 weeks, 12 weeks), and reported separately as adjusted mean differences in scores between the groups with 95% confidence intervals and 2-sided p-values. For secondary outcomes the same approach will be followed using linear mixed models to estimate and report the treatment effect at each time point. Cohen’s D effect sizes will be calculated as the adjusted mean difference of the outcome divided by the sample standard deviation of the outcome at baseline. These will be displayed in a forest plot showing the treatment effects on the primary and the secondary outcomes at 12 weeks. For the secondary analysis including 24-and 52-week time points, we will repeat the linear mixed model approach with these additional outcomes in the response vector. We will report the estimated marginal treatment effects at 24-and 52-weeks.

Missing data on individual measures will be pro-rated if more than 80–90% (depending on questionnaire) of the items are completed; otherwise, the measure will be considered as missing. We will check for differential predictors of missing outcomes by comparing responders to non-responders on key baseline variables. Any significant predictors will be included in the analysis models in a sensitivity analysis. This accounts for missing outcome data under a missing at random assumption, conditional on the covariates included in the model. As a sensitivity analysis, we will assess whether treatment adherence is associated with missing data, and if it is associated, use inverse probability weights or multiple imputation to compare results.

A pre-specified subgroup analysis will test the treatment effect in children (age < 18 years) by estimating the effect in each group separately. If the final proportion of under 18 s is low, we may use a Bayesian subgroup analysis to increase precision of the effect in the groups. There are no planned interim analyses.

For the mechanistic study, descriptive statistics for biomarkers at baseline and 12 weeks will be presented by treatment group. We will test for between-group differences on peripheral cytokines, GSH, brain glutamate and rCBF at 12 weeks using appropriate generalised linear models. Mechanistic analyses will be based on causal mediation analysis and the primary outcome variable will be the PANSS total score at 12 weeks. We will estimate the direct and indirect effects of clozapine on total PANSS via the mechanistic measures by fitting models for the outcome with and without mediators using the difference in coefficients approach, extended for multiple mediators. We will adjust for baseline values of the mediators [58] baseline PANSS total score, and fixed effects of sex, age, duration and number of previous treatment trials [59].

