Most of the evidence for the superiority of clozapine over other antipsychotics derives from studies in chronic patients; a recent meta-analysis found the median age in trials of clozapine to be 39 years with a median length of illness of 16 years [8]. Delay in initiating clozapine is associated with poorer response, and earlier use of clozapine and fewer pre-clozapine antipsychotic trials have been found to be associated with better treatment outcomes [13, 14]. The evidence for the efficacy of clozapine in younger patients is sparse, although it suggests that clozapine is superior to other antipsychotics in people under 18 with TRS [15], and that younger age is associated with greater symptom reduction in clozapine-treated people [16]. A recent retrospective study showed that the vast majority of paediatric patients (95%) admitted with or started on clozapine during an acute psychiatric hospitalization remained on clozapine at discharge, suggesting that it may be clinically effective [17]. Furthermore, a Danish cohort study on early onset schizophrenia showed that the majority of patients (88.8%) prescribed clozapine were considered as having a favourable response since they continued to redeem clozapine prescriptions for more than 6 months [18]. However, there are significant limitations of naturalistic, observation data such as these, including that clinicians may be unlikely to stop clozapine treatment once started given a perception it is a treatment of last resort [19]. There is thus a clear need for larger scale clinical trials in younger patients.

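### Duration of previous treatment enters the primary model as two categories split at 3 years; a continuous term would probably keep a little more precision at no cost

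*Protocol article*

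**What the plan says.** In the protocol's Statistical analysis section, the primary linear mixed model has fixed effects for sex, age group, "duration of previous treatment (± 3 years"), the baseline value of the outcome, treatment, time and their interaction. Number of previous antipsychotic trials is not among them, and no reason is given for cutting duration at 3 years.

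The same section adjusts the mediation analysis, whose outcome is PANSS total at 12 weeks, for baseline mediators, baseline PANSS and "fixed effects of sex, age, duration and number of previous treatment trials". It does not say whether duration is continuous or categorical there.

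Under Randomisation, "The sample will be stratified by sex and age group", with no mention of treatment history. Under Assessments, research assistants record the complete antipsychotic history, from which both duration and number of trials can be derived.

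The Introduction says "Delay in initiating clozapine is associated with poorer response" and that "fewer pre-clozapine antipsychotic trials have been found to be associated with better treatment outcomes".

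**The concern.** Age group appears in two categories because it is stratified that way. Duration has no such reason, so the 3-year cut is a free modelling choice. Cutting a continuous predictor treats everyone on one side of the cut as alike and usually discards part of what the predictor explains. The protocol does not say how participants aged 12 to 24 will divide at 3 years; if the division is far from even, more is lost. Number of previous trials is also available and is left out of the primary model.

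At stake is the width of the confidence interval for the primary PANSS comparison. Validity is not at stake.

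**Working it through.** **1. Reproduce the sample size.** Inputs from Sample size: the standardised difference "based on PANSS total score at 12 weeks is 0.39", baseline to 12-week correlation 0.5, attrition 20%. Allocation is 1:1 (Randomisation). Two-sided alpha of 0.05 is assumed from the 95% intervals and two-sided p-values in Statistical analysis. Power for the main trial is not stated.

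With adjustment for baseline, the residual SD in standardised units is √(1 − 0.5²) = 0.866. At 90% power, n per arm = 2 × [0.866 × (1.960 + 1.282) / 0.39]² ≈ 103.6, so 104 per arm and 208 in total. Allowing for attrition, 208 / 0.8 = 260, the stated target.

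An unadjusted or change-score calculation at 80% power also gives 260, so 90% is inferred. However the figure was derived, the stated inputs with baseline adjustment give 90.1% power at 104 per arm. The calculation credits only the baseline correlation and takes nothing from duration or number of trials. It treats the 12-week comparison as a simple baseline-adjusted one, which is enough for relative changes in precision.

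**2. What a split keeps.** For a normal covariate with a linear effect, cut so that a proportion p lies on one side, the share of explained variance kept is φ(z)² / [p(1 − p)], where z is the normal quantile of p:

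- 50/50: 0.3989² / 0.25 = 0.637
- 70/30: 0.576
- 80/20: 0.490
- 85/15: 0.2332² / 0.1275 = 0.426
- 90/10: 0.342

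**3. Gain from added explained variance.** The protocol gives no R² for either variable beyond baseline PANSS, so a range is assumed. The SE is multiplied by √(1 − R²), and power is recomputed at 104 per arm.

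| Added partial R² | SE ratio | Power | Equivalent recruited N |
|---|---|---|---|
| 0 | 1.000 | 90.1% | 260 |
| 0.01 | 0.995 | 90.4% | 258 |
| 0.02 | 0.990 | 90.7% | 255 |
| 0.05 | 0.975 | 91.5% | 248 |
| 0.10 (optimistic) | 0.949 | 92.8% | 235 |

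**4. The split alone.** Let linear duration explain R² of the residual variance. The split then gives up R² × (1 − share kept).

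| Duration R² | Lost at 50/50 | Power, split to linear | Lost at 80/20 | Power, split to linear |
|---|---|---|---|---|
| 0.02 | 0.007 | 90.5% to 90.7% | 0.010 | 90.4% to 90.7% |
| 0.05 | 0.018 | 91.0% to 91.5% | 0.026 | 90.8% to 91.5% |
| 0.10 | 0.036 | 91.9% to 92.8% | 0.051 | 91.5% to 92.8% |

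**5. Both changes together**, against a median split, with the two variables assumed to contribute independently. For (duration R², number R²) of (0.02, 0.01), power goes from 90.5% to 90.9%; for (0.03, 0.03), from 90.6% to 91.8%; for (0.05, 0.05), from 91.0% to 92.8%. Duration and number of trials probably overlap, so these are upper figures.

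**The case against.** The case against raising this at all is fair. A short, pre-specified covariate list is legitimate, randomisation keeps the treatment estimate unbiased with either list, and the benefit depends entirely on assumed correlations. The Introduction's statements concern outcome on clozapine. They do not show that either variable predicts 12-week PANSS under treatment as usual, or beyond baseline PANSS. If the relation exists only under clozapine, it is effect modification and a main-effect covariate gains less. Delay to clozapine is also not the same quantity as duration of previous treatment, the age limit may narrow its range, and a true step near 3 years would shrink the loss. All of this stands and limits the size of the point. It supplies no reason for preferring the cut.

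A reader might go further and infer that the primary and mediation models contradict each other, or that their total effects ought to agree. The protocol does not support that:

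- Mediators are not randomised, so a mediation analysis needs adjustment for common causes of mediator and outcome. A wider covariate set there is expected.
- The mediation analysis rests on about 70 participants with complete mechanistic data, against about 208 completers in the primary analysis, so the total effects would differ anyway.
- The form of duration in the mediation model is not stated. The documented difference in treatment-history covariates is number of trials only, and continuous duration cannot be said to match that model.

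A reader might also infer that the split undermines the sample size. It does not, because 260 is reached without any credit for duration.

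**Conclusion.** The point holds as a minor efficiency improvement. The 3-year split is not required by the design and, if the effect of duration is roughly linear, keeps about 64% of its explained variance at best and about 43% at 85/15. Under an assumed added partial R² of 0.01 to 0.05 (partial correlations of about 0.10 to 0.22, the square roots), the SE would fall by about 0.5% to 2.5% and power would rise by about 0.3 to 1.4 points from an inferred 90%. An optimistic R² of 0.10 gives about 5% and 2.7 points. The gain could be close to nothing if neither variable predicts outcome beyond baseline PANSS, and is smaller if the association is confined to the clozapine arm. There is no bias, no shortfall in the target of 260 and no inconsistency between models.

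**What to change.** In the statistical analysis plan, before any outcome data are seen by arm, specify duration of previous treatment as a continuous covariate in the primary model, with its transformation named in advance. A log scale is workable because eligibility requires two earlier trials of more than 6 weeks each, so duration cannot be zero. Consider adding number of previous antipsychotic trials. If the two-category form is kept, for example because start dates are expected to be unreliable, a sentence giving the reason is enough.

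The cost is one line of text. Continuous duration replaces the binary term without using an extra degree of freedom, number of trials uses one, and no new data are needed. The protocol's covariate list should be brought into line.

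### One baseline slope is fixed for every visit out to week 52; if it fades and drop-out depends on baseline differently by arm, the 24- and 52-week estimates are biased

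*Protocol article*

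**What the plan says.** All of this is in the protocol article, section Statistical analysis, unless another section is named.

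- The fixed effects are itemised: sex, age group, duration of previous treatment, then "baseline assessment for the outcome under investigation, treatment, time, and time*treatment interactions". Time by treatment is the only interaction.
- The random part is an intercept: "Participant will be included as a random intercept to account for repeated measures".
- The primary model uses the visits up to week 12 (weeks 6 and 12). For the longer follow-up, "we will repeat the linear mixed model approach with these additional outcomes in the response vector", and marginal effects at 24 and 52 weeks will be reported.
- On missing data: "This accounts for missing outcome data under a missing at random assumption, conditional on the covariates included in the model". The sentence before it adds significant predictors of missingness to the models as a sensitivity analysis. Weighting or multiple imputation follows only if adherence is associated with missingness.
- The Sample size section assumes a baseline to 12-week correlation of 0.5 and defends it by the shortness of the gap. No correlation is given for weeks 6, 24 or 52.

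**The concern.** A single baseline coefficient is a compromise across visits. The Sample size section's own argument is that a short gap supports a correlation of 0.5, which implies that a longer gap supports less. After week 12 treatment may change, and participants on usual treatment may start clozapine (Discussion), which may loosen the link with baseline further. If the slope does fade, the common slope is too steep at week 52.

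That alone does no harm to the estimate, because randomisation balances baseline. Harm arises when the participants still observed at a late visit differ in baseline between arms. The trial is open label and only the clozapine arm has weekly blood monitoring, so drop-out that depends on severity differently by arm is conceivable. The model then corrects the baseline gap with the wrong slope, and the error appears as a treatment difference.

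At stake are the 24- and 52-week estimates for PANSS and for other repeated scores with their own baseline. EQ-5D-Y is the clearest case, since the Aim and objectives section states hypotheses for it at those times. The planned missing-data steps do not cover this: adding a predictor as a main effect leaves the baseline slope constant, and weighting or imputation depends on adherence.

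**Working it through.** **1. The plan's own figure.** Inputs from Sample size: effect 0.39, correlation 0.5, 20% attrition; two-sided 5% inferred from the 95% intervals. The article does not state power for this figure; 90% reproduces it.

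n per arm = 2(1.960 + 1.282)² × (1 − 0.5²) / 0.39² ≈ 104, so 208 in total, and 208 / 0.80 = 260. The extra model term does not alter this.

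**2. The mechanism.** To a first approximation,

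bias at visit t ≈ (slope at t − common slope) × (baseline gap between the observed arms at t).

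Assume slopes 0.7/0.5/0.4/0.3 at weeks 6/12/24/52 (equal to the correlations if the SD is constant) and retention 0.9/0.8/0.7/0.6. The retention-weighted common slope is (0.63 + 0.40 + 0.28 + 0.18) / 3.0 = 0.497. With a baseline gap of −4.72 points at week 52, bias ≈ (0.3 − 0.497) × (−4.72) = +0.93. Simulation of the full random-intercept model gives +1.30 for that case, so the formula shows direction and order of size only.

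**3. Simulation, four-visit model, week 52.** SD 16.2 (the upper limit used in Sample size), cumulative drop-out 10/20/30/40%, n = 400,000 to expose bias. Drop-out strength is the log-odds per baseline SD. All correlations and drop-out strengths are assumptions, as is the loss after week 12.

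| Correlations | Drop-out and baseline | Baseline gap | Bias, common slope | Bias, visit-specific slopes |
|---|---|---|---|---|
| 0.7/0.5/0.4/0.3 | unrelated | 0.00 | −0.05 | −0.05 |
| 0.7/0.5/0.4/0.3 | 1.0 in both arms | −0.09 | −0.01 | −0.03 |
| 0.7/0.5/0.4/0.3 | 0.7 in one arm only | −4.72 | +1.30 | +0.12 |
| 0.7/0.5/0.4/0.3 | 0.5, opposite signs | −7.20 | +1.86 | +0.05 |
| 0.7/0.5/0.4/0.3 | 1.0, opposite signs | −12.42 | +3.12 | −0.04 |
| flat 0.5 | 1.0, opposite signs | −12.47 | +0.05 | +0.05 |

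Rows 1, 2 and 6 show that both conditions are needed. The sign reverses if the drop-out pattern reverses. An unstructured covariance with the same common slope does not help (+2.98 in row 5).

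**4. The range relied on.** Row 5 is extreme. With drop-out strengths from 0.4 in one arm only up to 0.8 with opposite signs, and a week-6 correlation of 0.6-0.7, the common-slope bias is:

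- week 12, two-visit primary model: about 0.1-0.8 points;
- week 52, correlation 0.3: about 0.7-2.5 points;
- week 52, correlation fading only to 0.45: about 0.2-1.4 points.

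I re-ran these cases and obtained the same ranges to within simulation noise of roughly 0.1 point. Visit-specific slopes gave values near zero throughout.

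Against the 12-week target ("an effect size of 0.39 corresponds to a between group difference of 6.4 points"), the week-12 range is 0.1/6.4 ≈ 2% to 0.8/6.4 ≈ 13%.

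**5. Cost without differential drop-out.** At n = 260 the empirical SD of the week-52 estimate is 2.45 with the common slope and 2.39 with visit-specific slopes: (2.45/2.39)² ≈ 1.05, about 5% of variance. At week 12 it is 1.91 against 1.90.

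**The case against.** **The sizes are assumed.** This stands. The only correlation in the article is baseline to 12 weeks, and nothing in it quantifies baseline-related drop-out by arm. The upper end needs sicker participants to leave one arm while less ill ones leave the other. Case-note review is the fallback at 24 and 52 weeks, so late losses may also be smaller than assumed.

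**A fading correlation is not a fading slope.** This also stands. The slope is the correlation times the ratio of the later SD to the baseline SD. Entry requires PANSS of at least 70, which restricts the baseline spread; if scores spread out later, the slope fades less. A reader might infer that the common slope is certainly too steep at week 52. The documents do not show that.

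**The consequence is easily overstated.** A reader might infer that the primary analysis is unsound or that all the 24- and 52-week hypotheses are at risk. Neither follows. The week-12 bias is small even under adverse assumptions. The article has no PANSS hypothesis at 24 or 52 weeks. Cost-effectiveness has its own bootstrap analysis, staying on medication is not a score with a baseline value, and follow-up CGI-Improvement has no baseline on the same scale. Nor should the week-52 bias be set against 6.4 points, which is a 12-week target.

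**The missing-data sentence can be read narrowly**, as describing the sensitivity analysis just before it. That is fair, so the article should not be read as making a false claim about the 52-week model. The gap remains, because that sensitivity analysis does not free the baseline slope.

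**This is detail for the analysis plan.** Partly so: that plan is not shown and may add the term, and a common slope is conventional. But the article itemises the model and carries it to 52 weeks, so the common slope is a stated choice.

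**Conclusion.** The point holds as a conditional weakness of the 24- and 52-week model. It needs both a baseline slope that weakens over the year and drop-out related to baseline differently by arm. Without either one there is no bias, and at most a small loss of precision.

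Under the stated assumptions the week-52 bias can be a point or two on PANSS, in either direction, while the primary endpoint is little affected. The same mechanism applies to EQ-5D-Y, but its size on that scale was not worked out. This is a minor, inexpensive improvement and not a defect that threatens the trial's main conclusion.

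**What to change.** In the 24/52-week model, add an interaction between time and the outcome's own baseline value, so that each visit has its own slope. Do the same in the 12-week model for consistency. One sentence in the statistical analysis plan is enough, settled before anyone sees outcome data by arm.

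The cost is 3 degrees of freedom in the four-visit model and 1 in the two-visit model. No new data are needed and N stays at 260. For outcomes with no baseline on the same scale, such as CGI-Improvement, the plan should say which baseline value, if any, enters the model.

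### The under-18 subgroup analysis estimates each age group separately and names no treatment-by-age interaction, so the plan has no direct estimate of whether the effect differs by age

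*Protocol article*

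**What the plan says.** The Statistical analysis section of the protocol article fixes the subgroup method in one sentence: a subgroup analysis, specified in advance, is to test the effect in under-18s "by estimating the effect in each group separately". If the share of under-18s turns out low, it adds, "we may use a Bayesian subgroup analysis to increase precision of the effect in the groups". It does not define low, and it names no prior or model for the Bayesian analysis.

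The same section lists the fixed effects of the mixed model. Sex, age group (cut at 18) and duration of previous treatment enter as main effects, followed by "baseline assessment for the outcome under investigation, treatment, time, and time*treatment interactions". The only interaction is between time and treatment.

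The Randomisation section stratifies by the same age cut. No section gives a target or expected number of under-18s. The Sample size section is for the whole trial and takes its effect from adults: "The standardised mean difference for clozapine versus other antipsychotics in adults based on PANSS total score at 12 weeks is 0.39".

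**The concern.** Separate estimates in two groups of unequal size have unequal power. If one is significant and the other is not, that pattern is weak evidence that the effects differ, because it is common when they are the same. The plan names a test in children and produces an adult result beside it, but names no estimate of the difference between them.

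This matters here because the Introduction presents the trial as filling an evidence gap on clozapine in young patients, and cites the guideline for children as well as the one for adults. The child result will be read closely. A non-significant child estimate next to a significant adult one could be taken as lack of benefit in children, when the smaller group alone would explain it.

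**Working it through.** **Inputs from the Sample size, Randomisation and Statistical analysis sections.** Standardised effect 0.39. SD of the 12-week PANSS: the article says it "is 14.2 (60% CI 12.96–16.20"), and it uses the upper limit, 16.2. Baseline to 12-week correlation 0.5. Attrition 20%, 260 recruited, allocation 1:1, two-sided p-values.

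**Assumptions.** Significance level 5% (suggested by the 95% CIs) and main-trial power 90%; neither stands in the sample size text. The share f of under-18s is not given, so a range is shown.

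**Step 1: reproduce the planned size.** Adjusting for baseline multiplies the variance by 1 − 0.5² = 0.75. Per arm, n = 2 × 0.75 × (1.960 + 1.282)² / 0.39² = 103.6, so 104. Total 208 evaluable, and 208 / 0.8 = 260. This matches the article.

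**Step 2: power in each age group under the same true effect.** The effective standardised effect is 0.39 / √0.75 = 0.450. Completers per arm are 104f in children and 104(1 − f) in adults. Power is from the noncentral t distribution. The two groups are independent, so P(adults significant, children not) = power in adults × (1 − power in children). At f = 25% there are 26 and 78 per arm, and 0.798 × (1 − 0.357) = 0.513.

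**Step 3: what the interaction can detect.** SE of the difference between the two effects = √0.75 × √(2/(104f) + 2/(104(1 − f))) in SD units. The difference detectable with 80% power is 2.80 × SE, converted to points with SD 16.2. At f = 25%, SE = √0.75 × √(2/26 + 2/78) = 0.277, and 2.80 × 0.277 = 0.777 SD = 12.6 points.

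| Under 18 (assumed) | Power, children | Power, adults | Adults significant, children not | Interaction detectable with 80% power |
|---|---|---|---|---|
| 10% | 16% | 87% | 72% | 18.2 points |
| 15% | 23% | 85% | 65% | 15.3 points |
| 25% | 36% | 80% | 51% | 12.6 points |
| 33% | 46% | 75% | 41% | 11.6 points |
| 40% | 53% | 70% | 33% | 11.1 points |
| 50% | 62% | 62% | 23% | 10.9 points |

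**Step 4: the same situation with an interaction test.** With equal true effects, a two-sided 5% interaction test falsely signals an age difference 5% of the time at any share. In simulation (1,000,000 draws per share, normal approximation), the pattern of adults significant, children not, and interaction significant occurred in 2.3% to 2.5% of trials. The test is weak, however. If the true effect were 0.39 SD in adults and zero in children, its power would be about 16% at a 10% share, 26% at 20% and 37% at 50%.

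**The case against.** The strongest case against is that the article claims no difference by age. Its hypotheses contain none, and the stated question, the effect in children, is answered by a within-child estimate. That stands. The harm arises only when the two results are compared, although reporting them together makes that likely.

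It can also be said that separate estimation does not rule out a shared model: age-specific effects could come from one model with an interaction, and the statistical analysis plan, which is not shown, may say so. It is therefore not established that separate models will be fitted. But the article does list its model terms, and treatment by age is not among them.

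Nor do separate estimates say nothing about a difference. Two independent estimates with CIs allow it to be computed, as Step 3 does. The plan just does not name it as a result.

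An interaction term does not raise power in children, and it will usually be imprecise. That is true, and it is a reason to report the interval and warn against reading non-significance as equality.

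Two stronger readings are tempting. A reader might infer that the Bayesian method is chosen after the data are in. The trigger is an enrolment proportion, which carries no information on outcome by arm, so the fair criticism is only undefined discretion. A reader might also infer that any age contrast is a rater contrast, because the Blinding section has two research psychiatrists, "one for adult participants and the other for child participants". Within an age group the same rater would score both arms, so a constant difference between raters cancels from each treatment effect and from the interaction. It could matter only if the raters differ in sensitivity to change, and the article gives no evidence of that.

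**Conclusion.** The point holds as a weakness in a stated method. The plan tests the effect in under-18s by separate estimation and names no direct estimate of a difference by age. With identical true effects, the misleading pattern would occur in roughly 23% to 72% of trials for under-18 shares from 50% down to 10%. These figures rest on 104 completers per arm, a correlation of 0.5, an effect of 0.39 SD in both groups, a 5% level and an assumed share.

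The primary analysis is unaffected. The documents do not support saying that the trial will claim a lack of effect in children, that the subgroup method depends on outcomes, or that age and rater effects cannot be told apart.

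**What to change.** - Fit one mixed model to all participants with treatment by time by age group, using the randomisation strata. Report the 12-week interaction with its 95% CI as the basis for any statement about a difference by age, and take both age-specific effects with CIs from that model.
- State that the interaction has 80% power only for about 11 to 18 points (shares of 50% to 10%), against the 6.4-point difference used for the whole trial. A non-significant interaction is then not evidence of equal effects, and a non-significant child estimate is not evidence of no effect in children.
- If Bayesian shrinkage is wanted, fix its model and prior, and either define the low share or use the analysis whatever the share, before outcome data by arm are seen.
- Optionally, note that one rater per age group could affect the interaction if the raters differ in sensitivity to change.

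The cost is a few sentences and slightly more analysis, with no new data. The downside is an interaction estimate that will usually be imprecise.
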